## Methods/design

### Trial design

This protocol is described according to SPIRIT guidelines for clinical trials ([25]). The trial is a two-arm pragmatic, comparative effectiveness RCT comparing flat flexible shoes to stable supportive shoes. It will be conducted at The University of Melbourne over 3 years. The primary end-point for analysis of outcomes is after 6 months of shoe wear.

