**Table 1 Tab1:**
[figure not shown]
Schedule of enrolment, interventions and assessments

Baseline assessments will be carried out at the Department of Physiotherapy, the University of Melbourne. At the 6-month follow-up, participants will complete questionnaires either on paper or electronically at home. Participants will also complete a short log book to record adherence with allocated footwear for one week of each month during the intervention period. If questionnaires or log books are not returned, the participant will be contacted by email and or phone to prompt their return, or as a last resort, to obtain primary outcome data. Ethical approval has been obtained from the University of Melbourne Human Research Ethics Committee (HREC No. 1748784). All participants will provide written informed consent.

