Secondary outcome measures will be administered at baseline and at 6 months unless otherwise indicated. These include:*Pain subscale of the KOOS*. The subscale is scored using 9 questions about knee pain experienced in the last week, with Likert response options from None to Extreme. Scores range from 0 to 100, with lower scores indicating worse pain [32].*Sport and recreation subscale of the KOOS.* The subscale is scored using five questions regarding function with sport and recreational activities in the last week, with Likert response options ranging from None to Extreme [32]. Scores range from 0 to 100, with lower scores indicating worse function [32].*Quality of life subscale of the KOOS*. The subscale consists of four questions about knee-related quality of life experienced in the last week, with five Likert response options for each question. Scores range from 0 to 100, with lower scores indicating worse quality of life [32].*Patellofemoral pain and OA subscale of the KOOS.* The subscale is comprised of 11 questions about knee pain and function experienced in the last week, with five Likert response options for each question. Scores range from 0 to 100, with lower scores indicating worse patellofemoral symptoms [33].*Lower limb pain severity*. Average overall pain in the last week will be recorded using an 11-point NRS (0 = no pain and 10 = worst pain possible) at each of the following sites: (i) study knee, (ii) contralateral knee, (iii) ipsilateral hip, (iv) contralateral hip, (v) ipsilateral foot/ankle, (vi) contralateral foot/ankle, and (vii) back.*Participant-perceived global change.* At 6 months, participants will rate their overall global change in a) pain and b) physical function since enrolling in the study. Response to treatment will be scored using a 7-point global rating of change Likert scale, with terminal descriptors of ‘much worse’ to ‘much better’ [34]. Participants who report ‘moderately better’ or ‘much better’ will be classified as improved. All other respondents will be classified as not improved.*Health-related quality of life.* The Assessment of Quality of Life (AQoL) [35] (version AQoL-6D) will be used to measure health-related quality of life. It consists of 20 items that assess independent living, mental health, relationships, pain, coping and senses. Scores range from − 0.04 to 1.00 with higher scores indicating better quality of life.*Physical activity levels.* The Physical Activity Scale for the Elderly (PASE) will be used to measure physical activity over the previous week [36]. Scores range from 0 to over 400, with higher scores indicating greater physical activity.

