
### Treatment adherence

Participants will rate their perceived overall level of adherence over the past 6 months with the instruction to wear their allocated shoes for a minimum of 6 h per day on an 11-point NRS (with terminal descriptors of ‘shoes not worn all’ and ‘shoes worn completely as instructed’). At the 6-month follow up assessment, participants will also indicate whether they stopped wearing either pair of study shoes during the 6 months on a categorical scale (Yes or No). Participants who score Yes will describe when and why they ceased wearing their allocated shoes, and this will be reported descriptively. Finally, participants will record in log books how many hours each day they wear their allocated shoes, for 7 consecutive days every month, over the 6-month intervention period.

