### Adverse effects of treatment and co-interventions

Adverse events will be defined as any problem experienced in the study knee or elsewhere in the body because of wearing the study shoes. Adverse events will be self-reported by participants using a custom-developed table, and by open-ended questioning at 6 months. Participants will also be asked to contact the researchers at any time by telephone or email to report adverse events. Use of co-interventions (medications for knee pain and any other treatments for knee OA) will also be recorded at baseline and 6-months. Participants will complete a custom-developed table to indicate the frequency of use (over the past 6 months) of a range of pain and arthritis medications and co-interventions.

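### In the text shown, adverse events are solicited only at 6 months, so early, transient shoe problems that participants do not volunteer depend on up to 6 months' recall

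*Protocol article*

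**What the plan says.** The section on adverse effects and co-interventions sets out two routes. The solicited route is: "Adverse events will be self-reported by participants using a custom-developed table, and by open-ended questioning at 6 months". The unsolicited route follows directly: "Participants will also be asked to contact the researchers at any time by telephone or email to report adverse events". An adverse event is defined by attribution to the footwear: "Adverse events will be defined as any problem experienced in the study knee or elsewhere in the body because of wearing the study shoes".

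The Trial design section places the outcome assessment at the end of the wear period: "The primary end-point for analysis of outcomes is after 6 months of shoe wear". The Procedure section describes no follow-up assessment before that.

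Participants do record something every month. The Procedure section says: "Participants will also complete a short log book to record adherence with allocated footwear for one week of each month during the intervention period". The Treatment adherence section gives the content: "participants will record in log books how many hours each day they wear their allocated shoes, for 7 consecutive days every month". No adverse event item is described for the log book.

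Two other month-6 measures bear on harms:
- Participants say whether they stopped wearing either pair. For those who did: "Participants who score Yes will describe when and why they ceased wearing their allocated shoes, and this will be reported descriptively".
- Pain is scored at the knees, hips, feet/ankles and back, at baseline and 6 months: "Average overall pain in the last week will be recorded using an 11-point NRS".

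**The concern.** The expected harms of a footwear trial are mostly minor and may come early, while the participant adapts to a new shoe. These are also the problems most easily forgotten. If they are asked about once, at the end of the wear period, some will be lost from the counts in both arms, and onset and duration will be dated from memory.

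Loss that is equal in both arms lowers the counts but leaves the direction of the comparison intact. Loss that differs between arms distorts the comparison. That could happen if problems tend to come early in one shoe class and late, or persistently, in the other. The Background says that stable supportive styles are what people with knee osteoarthritis typically wear, so the flat flexible arm may on average make the larger change of footwear. Different onset timing is therefore conceivable, but this is an inference and the document does not state it.

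The trial is meant to inform footwear advice, and tolerability is part of such advice. The point concerns when events are collected, not the attribution rule in the definition.

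**Working it through.** The plan gives no figure on this point to reproduce. The check is a comparison of the capture routes, followed by an illustration on assumed inputs.

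**Step 1: what each route catches.** Take a participant with foot pain from week 3 that has cleared by month 3.
- *Phone or email at any time:* captured as it happens, but only if the participant makes contact.
- *Month-6 table and open question:* captured only if remembered, about 3 months after it resolved.
- *Month-6 question on stopping:* captured only if a pair was abandoned, and again from memory.
- *Site pain scores:* not captured, because they cover the week before baseline and the week before month 6.
- *Monthly log book:* not captured as described, because it records hours of wear.

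So an event that is transient, not volunteered and not a cause of stopping has one route left, the month-6 enquiry. Its recall window is 0 to 6 months.

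**Step 2: what a gap between arms would require.** The document gives no event rate, recall loss, onset timing or volunteering rate. All four below are assumptions.
- True event rate p = 30% in both arms.
- Recall loss of 5% to 15% per month. A month-1 event asked about 5 months later is recalled with probability r = 0.95^5 = 0.774 down to 0.85^5 = 0.444. A month-6 event is recalled fully.
- d = the difference between arms in the share of events that fall in month 1, the rest falling in month 6.
- v = the share of events volunteered when they happen, the same in both arms and at both times.

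Spurious gap in observed rates = p × d × (1 − r) × (1 − v).

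- *Same timing in both arms (d = 0):* gap = 0, although both counts are too low.
- *60% versus 40% in month 1 (d = 0.2), none volunteered (v = 0):* 0.30 × 0.2 × 0.226 = 1.4 points, up to 0.30 × 0.2 × 0.556 = 3.3 points.
- *All in month 1 in one arm, all in month 6 in the other (d = 1), v = 0:* 0.30 × 0.226 = 6.8 points, up to 0.30 × 0.556 = 16.7 points.
- *Any of these with half volunteered (v = 0.5):* the gap is halved, for example 3.4 to 8.3 points in the extreme case.

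The result runs from nothing to about 17 points depending wholly on inputs that the document does not supply. The illustration shows the mechanism and is not an estimate.

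**The case against.** The case on the other side is substantial.

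- **Participants are told to report at any time.** A reader might infer from the single solicited time point that all early or resolved problems rest on 6-month recall. The documents do not support that, since the sentence after the quoted one opens a route throughout the wear period. This stands, and it limits the point to events that are not volunteered.
- **Stopping is asked about specifically.** The question on when and why shoes were abandoned is a targeted cue for the events that matter most to tolerability. This stands in part: it is asked at month 6 and leaves out people who had a problem and kept wearing both pairs.
- **Material is missing.** Table 1 and the log book form are not shown, and the month-6 time point may grammatically attach only to the open-ended questioning, leaving the timing of the table unstated. An earlier prompt cannot be excluded. This stands as a caveat on the whole point.
- **Monthly log completion is not monthly contact.** Nothing says that logs are returned each month or that staff speak to participants then. A reader might count six contacts with the centre already in place, but only six log weeks are described. This stands.
- **A large gap needs an extreme split of onset timing.** This stands: the upper figures in Step 2 require opposite timing in the two arms and no volunteered reports.
- **Asking repeatedly has its own effect.** In a limited-disclosure trial with self-reported outcomes, monthly questions on shoe problems may draw attention to symptoms. This stands as a real, probably small, cost that identical wording in both arms makes even.

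What survives is that, in the text shown, nobody asks before month 6, and no other described measure catches an early, transient problem that the participant neither reports nor stops the shoes for.

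**Conclusion.** The point holds in a narrow form. In the text shown, solicitation of adverse events is fixed at 6 months and capture before then is passive. Early, transient problems that are not volunteered rest on up to 6 months' recall and may be under-counted. The under-count could be uneven if onset timing differs between the shoe classes.

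Its size cannot be derived from the document. On the assumed inputs above, the spurious gap is zero with equal timing, 1.4 to 3.3 points with a 60/40 split, and 7 to 17 points only in an extreme case that nothing in the document establishes.

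This is a limitation of harms ascertainment and a cheap improvement. It is not a contradiction or a wrong figure, and it leaves the primary analysis and the sample size untouched. It rests on the assumption that Table 1 and the log book form contain no earlier adverse event prompt. If they do, the point falls away and the sentence on timing needs only to be clarified.

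**What to change.** Add a brief adverse event item to the log book already completed for one week each month, worded identically in both arms: site, onset, effect on shoe wear, and whether resolved. Ask about the time since the previous log as well as the log week, so that the recall window falls from up to 6 months to about one month.

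Keep the month-6 table and open-ended question as the closing report. Count each event once across log book, phone or email contact, and the month-6 report. Present events by arm and month of onset. State when the adverse event table is completed.

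Monthly return of the log books is optional. Recording at the time reduces recall loss even if the books come back at the end. Monthly return or electronic entry would also let the centre learn of problems during wear, but someone would then have to chase and read the forms.

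If the change is made while recruitment is under way, report events separately for participants enrolled before and after it.

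The cost is one short form and an ethics notification, slightly more participant burden and data entry, higher reported event counts in both arms, and some added attention to symptoms. No extra visits are needed.

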### Descriptive measures

A range of other measures will be collected to describe demographic characteristics, treatment expectations, self-efficacy, foot biomechanics and current footwear characteristics. These measures will not be used to determine treatment efficacy but will be used for descriptive purposes. They include height, weight and body mass index; radiographic disease severity using the Kellgren & Lawrence scale [27]; current employment status; a rating of participant expectation of treatment outcome, measured on a 5-point ordinal scale; self-efficacy, determined using the Arthritis Self Efficacy Scale [37]; objective measures of foot posture, mobility and function including the Foot Posture Index (FPI [38]), Foot Mobility Magnitude [39], navicular drop [40] and in-shoe regional foot pressure patterns (Novel Pedar, Munich, Germany) during walking; and characteristics of each participant’s three most commonly worn shoes, including shoe weight, heel height, pitch, motion control properties and flexibility [18].

### Sample size calculations

We aim to detect the minimal clinically important difference (MCID) on primary outcomes between groups (1.8 (out of 10) [41] for NRS pain and 6 (out of 68) for WOMAC function) [42]. We assume between-participant standard deviations of 2.7 and 11.4, and baseline to 6-month correlations of 0.21 and 0.39 for pain and function respectively (data from our footwear trial in a similar sample) [43]. Using analysis of covariance adjusted for baseline score, we need 46 per arm to achieve 90% power to detect MCID in pain and 65 per arm for function. Allowing for 20% attrition, we will recruit 82 people per arm (*n* = 164).

### Statistical analyses

A biostatistician will analyse data in a blinded manner, with *p* values less than 0.05 considered significant. Main comparative analyses between groups will be performed using intention-to-treat. If more than 5% of primary outcomes are missing, multiple imputation will be applied. For the primary hypothesis, differences in mean change in pain and function (baseline minus follow-up) will be compared between groups using linear regression modelling adjusted for baseline values and the stratifying variable of Kellgren & Lawrence grade. Similar analyses will be conducted for continuous secondary outcomes. Improvement based on global change will be compared across groups using risk differences, calculated from fitted logistic regression models. The effect of patient characteristics on outcomes will be explored by including relevant terms as covariates in models. Standard diagnostic plots will be used to check model assumptions.

To assess whether the effect of shoe class on the primary outcomes is moderated by any of Kellgren & Lawrence grade, Foot Posture Index score, body mass index or baseline score on the KOOS patellofemoral pain and OA subscale, appropriate interaction terms between randomised group and each of these variables will be included in regression models for the primary outcomes, and for each potential effect modifier separately. For the continuous moderators, a fractional polynomial approach will be applied [44].

### Timelines

The application for project funding was successful in October 2016 and funding commenced in August 2017. Ethics approval was obtained from the Human Research Ethics Committee of the University of Melbourne in May 2017. Recruitment commenced in August 2017 and will be completed in December 2019. The trial is due for completion in July 2020 when all participants will have completed 6-month follow-up.

## Discussion

This paper has outlined the theoretical foundation, and presented the protocol, for a two-arm pragmatic, comparative effectiveness RCT comparing flat flexible to stable supportive shoes for people with knee OA. Clinical OA guidelines recommend appropriate footwear for knee OA self-management [4, 8], with some guidelines specifying shoes with supportive features, based solely on expert opinion [8]. Stable supportive footwear are also recommended by clinicians for people with knee OA, and are typically worn by people with the disease [21]. Yet these styles increase knee loads compared to flat flexible shoes [18–20], while limited clinical data suggests flat flexible shoes may lead to symptomatic benefits [23]. Given the lack of high quality RCTs comparing footwear styles, leading international organisations [4, 8] have highlighted footwear clinical trials as an important OA research priority. Findings from the Footstep trial will assist clinicians and patients with knee OA in selecting the most appropriate footwear to help self-manage symptoms associated with the disease.

## Abbreviations

AQoL: Assessment of Quality of Life
CONSORT: Consolidated Standards of Reporting Trials
HREC: Human Research Ethics Committee
KOOS: Knee Injury and Osteoarthritis Outcome Score
MCID: Minimal clinically important difference
NRS: Numerical rating scale
OA: Osteoarthritis
PASE: Physical Activity Scale for the Elderly
RCT: Randomised controlled trial
WOMAC: Western Ontario and McMaster Universities
